### Inclusion Criteria

1. Age Between 18 and 70 Years old;2. Within 72 H From the Onset of Abdominal Pain;3. Symptoms and Signs of AP Based on Abdominal Pain Suggestive of AP, Serum Amylase at Least three Times the Upper Limit of Normal, and/or Characteristic Findings of AP on Computed Tomography or Less Commonly Magnetic Resonance Imaging (MRI) or Transabdominal Ultrasonography According to the Revised Atlanta Criteria (21).4. When Enrolled, TG > 1,000 mg/dL (11.3 mmol/L), Accompanied by the Clinical Features of any one or More of the Following (22):1) Signs of hypocalcemia (calcium levels < 2 mmol/L);2) Lactic acidosis (Lactate levels more than 2 mmol/L and PH < 7.35);3) The systemic inflammatory response syndrome (SIRS) is clinically recognized by the presence of two or more of the following:a) Temperature >38.5°C or <35.0°C;b) Heart rate of >90 beats /min;c) Respiratory rate of >20 breaths/min or PaCO2 of <32 mmHg;d) WBC count of >12, 000 cells/mL, <4,000 cells/mL, or >10 percent immature (band) forms;4) Organ failure defined by the sequential organ failure assessment (SOFA) score for respiration, renal and cardiovascular systems.

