### Primary Outcome Measure

The primary outcome is organ failure (OF) free days to 14 days after enrollment. Only the final period of OF-free days is included, and patients who have OF at day 14 or died before day 14 are assigned to zero OF-free days.

Secondary outcome measures

Part I: Secondary outcomes during the index admission

New-onset organ failure;New-onset multiple-organ failure (MOF);New-onset persistent organ failure (POF);New receipt of organ support;Requirement of ICU admission;ICU free days to day 14;Hospital free days to day 14;

Part II: Secondary outcomes within 60 days after enrollment

Mortality censored at 60 days after enrollment;AP severity grade (Based on the Revised Atlanta Classification);Incidence of infected pancreatic necrosis (IPN);Incidence of septic shock;Incidence of abdominal bleeding;Incidence of gastrointestinal fistula.

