### Definition of Outcomes

An individual SOFA score of 2 or more for the respiration, cardiovascular, or renal system is defined as the presence of organ failure. New-onset organ failure is defined as organ failure that is not present at any time in the 24 h after enrollment. Multiple organ failure is defined as two or more organ failures present at the same time. Persistent organ failure is defined as organ failure that persists for more than 48 h. ICU free days to day 14 after enrollment is defined as the number of days alive and not admitted to an ICU after the patient's latest discharge from the ICU before day 14. If the patient is admitted to an ICU on day 14 or dies prior to day 14, ICU-free days will be 0. Hospital-free days to day 14 after enrollment is defined as the number of days alive and not admitted to the hospital after the patient's final discharge from the hospital before day 14.

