### Statistical Analysis

Continuous normally distributed data were reported as means with SDs. Skewed continuous data were reported as medians and interquartile ranges (IQRs). Categorical data will be summarized by counts and percentages. The intergroup difference will be compared by Student's *t*-test or Wilcoxon rank-sum test for continuous variable depending on their normality and chi-square test for categorical data.

To evaluate the association between TG decline and OF free days, the study patients will be dichotomized depending on whether the TG level reaches 5.65 mmol/L on Day 3 (the day of enrollment is labeled Day 1, the next day labeled Day 2, and the following day Day 3). For the primary outcome comparison, Wilcoxon rank-sum test will be employed. However, since OF could be evaluated with a time-to-event analysis censored at 14 days to account for the mortality as a competing event, Fine and Gray competing risk regression is used to assess the group difference as a supportive analysis.

For the association between different TG lowering therapy and OF free days, we considered the possibility that baseline characteristics, which were expected to be prognostic for OF, differ according to the choice of TG lowering therapies (i.e., blood purification treatment and medical treatment). A propensity score matching will be further used to compensate for the intergroup unbalance.

For secondary outcomes, a multivariate analysis generalized linear model (GLM) model will be performed to identify its association with TG decline and TG-lowering therapy with proper link and distribution function. The variable included in the model will be age, sex, TG level at enrollment, and other baseline variables that have significant differences between groups.

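### The supportive Fine and Gray analysis of OF would count events that precede the Day-3 grouping, in a cohort that admits patients already in organ failure

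*Protocol article*

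**What the plan says.** All references are to the protocol article.

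- **Supportive analysis (Statistical Analysis).** The plan states that "OF could be evaluated with a time-to-event analysis censored at 14 days to account for the mortality as a competing event", and that "Fine and Gray competing risk regression is used to assess the group difference as a supportive analysis". The outcome is named only as OF. The text states no restriction to patients free of OF and no start of follow-up later than enrolment.
- **Groups (Statistical Analysis).** Patients are split by whether TG reaches 5.65 mmol/L on Day 3, with the day of enrolment counted as Day 1.
- **Entry (Inclusion Criteria).** High TG must be "Accompanied by the Clinical Features of any one or More of the Following", and the fourth feature is "Organ failure defined by the sequential organ failure assessment (SOFA) score for respiration, renal and cardiovascular systems". Organ failure alone is therefore enough.
- **Outcome definition (Definition of Outcomes).** The rule for OF reads: "An individual SOFA score of 2 or more for the respiration, cardiovascular, or renal system is defined as the presence of organ failure". This describes a prevalent state in the same three organ systems as the entry feature.
- **Incident OF (Definition of Outcomes).** It is defined separately: "New-onset organ failure is defined as organ failure that is not present at any time in the 24 h after enrollment". It is a secondary outcome and is not the term used for the Fine and Gray model.
- **Primary outcome (Primary Outcome Measure).** OF-free days to day 14, where "Only the final period of OF-free days is included"; OF at day 14 or earlier death scores zero.

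**The concern.** A time-to-event model needs an event that has not yet happened when follow-up starts, and groups that are known at that moment. Here the state that can qualify a patient for the cohort is also the outcome being timed, and the group label is fixed only on Day 3. Organ failure at entry, and its onset or recovery before the Day-3 TG measurement, can therefore enter the model as outcome information that is older than the grouping.

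The primary outcome is also counted from enrolment, so early OF feeds into both analyses. If patients with OF at entry or in the first days are less likely to reach the TG target, both results would lean the same way. Their agreement would then look like corroboration when part of it is shared early OF status.

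**Working it through.** **1. The plan's own figures.** Evaluable patients: 300 × (1 − 0.20) = 240. The stated power reproduces if one assumes two-sided alpha 0.05 and 120 per group, neither of which is stated. With power ≈ Φ(δ / (σ√(2/120)) − 1.96):

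- 2 days, SD 5: 2 / (5 × 0.1291) = 3.098, giving Φ(1.138) = 87.3% (t-test 87.0%; stated 87%).
- 1.5 days, SD 4: 1.5 / (4 × 0.1291) = 2.905, giving Φ(0.945) = 82.8% (t-test 82.5%; stated 82.5%).

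These figures concern a mean difference in OF-free days and do not bear on the Fine and Gray model. Only the 240 is used below.

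**2. Three possible events.** The text says only OF. Time is taken from enrolment, as for the primary outcome.

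- *Onset of OF.* Patients enrolled in OF have the event at or before time zero. Either they are dropped, so that the population differs from that of the Wilcoxon comparison, or they count as events at time zero. Patients whose first OF falls between enrolment and Day 3 have the event before they can be classified.
- *Recovery from OF.* Patients never in OF have nothing to recover from and do not belong in the risk set. Patients who recover before Day 3 have the event before classification.
- *Start of the final OF-free period.* Every patient can be given a value. Patients never in OF reach the event at enrolment, and patients who recover for good before Day 3 reach it before classification.

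Under each reading, some events precede the group definition. A patient who dies before the Day-3 measurement has no Day-3 TG value to be classified by.

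**3. Does the new-onset definition cure this?** No. It is not the event named for this model. Its 24-hour window also ends on the day labelled Day 2, so onsets between then and the Day-3 measurement would remain.

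**4. Size.** The share with OF at entry is not given. Assuming 20%, 40% or 60% of 240:

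- OF at entry: 0.20 × 240 = 48; 0.40 × 240 = 96; 0.60 × 240 = 144.
- At risk of a first OF at entry: 240 − 48 = 192; 240 − 96 = 144; 240 − 144 = 96.

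Under the onset reading, 48–144 patients have no valid event time. Under the final-period reading the problem moves to those free of OF at entry: of these 96–192, all who stay free of OF have the event at time zero. Events between enrolment and Day 3 come on top and cannot be sized from the document.

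**The case against.** The strongest reply has four parts.

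- **A whole-cohort event can be built.** A reader might infer that no single time-to-event outcome exists for this cohort. That goes too far: the start of the final OF-free period, with death competing and censoring at day 14 for those still in OF, gives every patient a value and fits the primary outcome's definition. This stands. It does not remove the timing problem, because that event also falls at enrolment or before Day 3 for some patients.
- **This is an article, and the analysis gets one sentence.** Naming the event and the time origin may be left to a fuller document. That stands too, and an unnamed event is not the point made here. The point is that the article itself fixes the Day-3 grouping, the day-14 horizon, the competing event and the entry criterion, and that these conflict under each reading.
- **Early OF may follow a TG decline already under way.** The exposure of interest is TG decline, and Day 3 is where it is classified. A reader might infer that OF in the first days can have nothing to do with it; the documents do not support that. What holds is narrower: OF present at entry precedes any decline under study, and OF before Day 3 precedes the classification and may itself influence who reaches the target.
- **The size is assumed.** No figure for OF at entry is given, so it cannot be said that the hazard ratio would mostly reflect entry status, only that it would partly do so.

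**Conclusion.** The point holds for the supportive analysis. Run from enrolment on the whole cohort, the Fine and Gray model would include events that precede the Day-3 grouping, whichever of the three events is meant. Its hazard ratio would partly reflect that earlier OF status and could appear to confirm the primary result.

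The extent is unknown. The 48–144 of 240 rests on an assumed 20–60% with OF at entry, and the direction of any distortion depends on how early OF relates to reaching the TG target, which the document does not report.

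A reader might infer that the primary result is undermined. This point does not show that: the Wilcoxon comparison of OF-free days is not changed by it. The analysis concerned is labelled supportive, in an observational study meant to inform later trials. The change is worth making before the data are analysed, but its reach is limited.

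**What to change.** Restate the supportive analysis as follows.

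- **Time origin.** Start at the Day-3 landmark, in patients alive with a Day-3 TG value. First reconcile the day labels: the Table 1 footnote calls the day of enrolment Day0, whereas Statistical Analysis calls it Day 1, so Day 3 in the latter is Day 2 in Table 1.
- **Patients free of OF at the landmark.** Event: first new OF. Competing event: death without OF. Censor at day 14.
- **Patients with OF at the landmark.** Event: sustained OF resolution. Competing event: death. Censor at day 14. Report this separately.
- **Adjustment.** Name baseline covariates, such as age, sex and TG at enrolment (already listed for the GLM) together with baseline SOFA. The primary Wilcoxon test has no covariates to carry over.
- **Interpretation.** Present both results as conditional on OF status at Day 3, which is a post-enrolment state that TG decline may itself affect. Do not present either as a direct mirror of OF-free days.

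The cost in work is analysis wording, since daily SOFA and daily TG are already collected. The statistical cost is smaller risk sets. As a rough guide only, suppose 96–192 patients are at risk and 20–40% of them develop new OF (both assumed). Events then range from 96 × 0.20 = 19.2 to 192 × 0.40 = 76.8. With power ≈ Φ(√(events/4) × |ln HR| − 1.96), equal groups and a hazard ratio of 0.5, power is about 33% to 86%. The landmark risk set will differ from the one at entry, so these figures should not be read as a forecast.

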### Study Population

Recruitment started on November 1st, 2020, and is scheduled to end on October 31st, 2022. This study is planned to recruit patients admitted to 30–40 hospitals across China. All adult patients presenting with early HTG-AP with worrisome features would be consecutively enrolled. The definition for HTG-AP with worrisome features is indicated as below.

All adult patients with AP admitted to the participating centers will be assessed for eligibility after admission (Figure 1). The inclusion and exclusion criteria are as follows:

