### Sample Size Justification

Based on the feasibility and patient flow of the participating sites, a sample size of 300 patients was expected, with an average of 15 patients per month within 2 years. Considering an estimated 20% rate of incomplete data or losses of follow-up, our expected sample size (240 patients) would provide 87% to detect a 2-days (SD: 5) or 82.5% for 1.5-days (SD: 4) improvement of organ failure free days between patients achieve target TG and those not.

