For blood purification, several studies assessed the effect of plasmapheresis on TG reduction and clinical outcomes. A systematic review involving eight studies found that it is effective in reducing TG level with a 69.6% decrease after treatment (14). Two studies reported a reduction of APACHE-II scores before and after plasmapheresis, while another retrospective study found plasmapheresis did not decrease morbidity or mortality (30–32). Based on the current evidence, HTG-AP is a category III, grade 2C indication for therapeutic plasma exchange in the American Society for Apheresis (ASFA) guidelines (15). Hemoperfusion (HP) is another blood purification modality that can absorb large pathogenic molecules from circulation by adsorbent materials installed in the HP cartridge. Hemofiltration is another choice, which was reported to be beneficial for AP patients (33, 34). However, there are no studies that have demonstrated the benefits of HP among HTG-AP patients by now. For other modalities, an RCT by He et al. (18) found that high-volume hemofiltration (HVHF) can lower TG levels more efficiently than insulin/heparin therapy but cannot improve clinical outcomes. A small pilot study enrolled 20 HTG-AP patients undergoing conventional treatment alone (the control group) or combined HVHF and HP treatment. The results showed a more significant reduction of TG level and improved clinical outcomes in the latter (35).

Taken together, there is no high-quality evidence demonstrating the clinical benefits of any specific TG-lowering therapy, and the primary choice of treatment varies significantly among different centers. In the 2021 Chinese guideline, TG lowering therapy, including fasting, medical treatment, and blood purification, are recommended when TG level is higher than 11.3 mmol/L. But the quality of evidence is moderate. Moreover, there are no clear recommendations regarding speficific TG-lowering therapy both in Chinese and international guidelines (23, 24, 36–38). The present study is designed to describe the current practice of TG-lowering therapy in HTG-AP and provide necessary data for future trials.

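### The therapy comparison is adjusted by matching for organ-failure-free days but by a separate GLM with significance-selected covariates for the secondary outcomes; one overlap-weighted analysis would be consistent and more precise.

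*Protocol article*

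**What the plan says.** All of this is in the protocol article.

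- **Therapy and OF-free days (Statistical Analysis).** The authors expect prognostic baseline characteristics to differ between blood purification and medical treatment, and respond: "A propensity score matching will be further used to compensate for the intergroup unbalance". Match ratio, caliper and propensity covariates are not given.
- **Therapy and secondary outcomes (same section).** "For secondary outcomes, a multivariate analysis generalized linear model (GLM) model will be performed", to cover both triglyceride decline and therapy. Age, sex and enrolment triglyceride are fixed covariates; any other baseline variable enters if it differs significantly between the groups. The analysis set is not stated.
- **Size (Sample Size Justification).** 300 patients are planned. "Considering an estimated 20% rate of incomplete data or losses of follow-up", 240 are expected to be evaluable. The stated power is for OF-free days "between patients achieve target TG and those not", not for the therapy groups.
- **Setting.** Study Population foresees 30–40 hospitals. The Discussion says that the preferred treatment differs markedly from centre to centre. Centre is not among the fixed GLM covariates.
- **Status (Study Objectives).** The therapy association is a secondary objective, and secondary endpoints are described as hypothesis generating.

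**The concern.** One contrast receives two adjustment methods, with no reason given and no common target population named. Matching estimates an effect in patients who find a match. A GLM, unless restricted to that set, estimates one in everybody. The covariate rules may differ as well, and the GLM's is data-driven: a significance test of baseline imbalance reflects sample size as much as prognostic importance, so a strong confounder can be left out and a harmless variable let in.

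If blood purification looked favourable on OF-free days but not on mortality, a reader could not tell a clinical difference from a change of method, patients or covariates. Matching also spends patients in a modest cohort, on a comparison intended to inform later trials.

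**Working it through.** **1. The plan's own figure.** Power = Φ(δ / (SD·√(1/n₁ + 1/n₂)) − 1.96). Two-sided α = 0.05 and a 120:120 split are assumed, since neither is stated.

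- Evaluable patients: 300 × 0.8 = 240.
- 2 days, SD 5: 2 / (5·√(2/120)) = 3.098; Φ(1.138) = 87.3%.
- 1.5 days, SD 4: 1.5 / (4·√(2/120)) = 2.905; Φ(0.945) = 82.8%.

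The noncentral t version gives 87.0% and 82.5%. The stated 87% and 82.5% reproduce, but they belong to the triglyceride-target comparison.

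**2. What 1:1 matching discards at best.** Assume that all 240 patients fall into one of the two therapy groups and that every patient in the smaller group finds a match. With share s in the smaller group there are 240s pairs, and 240 − 480s patients are unused. Power is for 2 days (SD 5). The variance ratio, before any inflation from weights, is [2/(240s)] / [1/(240s) + 1/(240(1−s))] = 2(1−s).

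| Split | Pairs | Unused | Power, matched | Power, all kept | Variance ratio 2(1−s) |
|---|---|---|---|---|---|
| 50/50 | 120 | 0 | 87.3% | 87.3% | 1.0 |
| 40/60 | 96 | 48 | 79.1% | 85.9% | 1.2 |
| 30/70 | 72 | 96 | 67.0% | 81.1% | 1.4 |
| 20/80 | 48 | 144 | 50.0% | 69.8% | 1.6 |

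This is only a guide. A caliper loses further pairs, while weighting inflates the variance of the all-patients estimate. If only 80% of the smaller group is matched, the unused count runs from 48 (50/50) to 164 (20/80).

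**3. Matching against overlap weighting.** Simulation takes both effects into account. Assumed: 240 patients, smaller-group share 20–50%, 1:1 matching, caliper 0.2 SD of the logit.

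- Pairs kept: 43–87, so 240 − 2×43 = 154 down to 240 − 2×87 = 66 patients unused.
- Variance ratio, matched to overlap-weighted: 1.14–1.53, with both estimates near unbiased.
- In standard-error terms: √1.14 = 1.07 to √1.53 = 1.24, so intervals about 7–24% wider.
- Equivalent loss of patients: 1 − 1/1.14 = 12% to 1 − 1/1.53 = 35%.

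A simulation with four assumed confounders gave ratios of 1.26–1.44 for shares of 25–40% and 1.19 at 50%. There, overlap weighting was as precise as full covariate adjustment (standard errors 0.65–0.72 day for both).

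**4. Would filling in details remove the split?** A caliper, ratio and covariate list in an analysis plan would complete the matching. They would not change the published assignment of matching to one outcome and a significance-driven GLM to the others.

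**The case against.** **Much of the detail is unstated, and an article may leave it to the analysis plan.** This stands. The propensity covariates are not listed, so neither a different covariate set nor the absence of a given confounder from the propensity model can be shown. The GLM's analysis set is not stated either. The whole cohort is the natural reading, because the same GLM also serves triglyceride decline, where no matching is planned, but it is an inference.

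**Matching is standard and valid.** Also true: both methods were near unbiased. At an even split with complete matching nobody is lost. Matching is to be used in addition, so an unmatched comparison may be reported too. The two methods can target somewhat different populations, so part of the variance gap may reflect a changed estimand. What remains is a gain in precision and consistency, not the correction of an invalid analysis.

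**A stronger reading: calendar time confounds the comparison.** Recruitment spans a guideline's year: "Recruitment started on November 1st, 2020, and is scheduled to end on October 31st, 2022", and "In the 2021 Chinese guideline, TG lowering therapy, including fasting, medical treatment, and blood purification, are recommended" above the study's own entry threshold. A reader might infer a shift towards blood purification during recruitment. The documents do not support this. The guideline names both therapies, and the Discussion goes on to say that neither Chinese nor international guidelines clearly favour a specific one. Suppose blood purification rose from 25% to 45% and 60% of patients enrolled afterwards. Late enrolments would be 0.6×0.45/(0.6×0.45 + 0.4×0.25) = 73% against 0.6×0.55/(0.6×0.55 + 0.4×0.75) = 52%, about 0.2 day of bias per 1-day secular change. Every one of those inputs is assumed. Centre is the better documented omission from the fixed GLM covariates.

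**Conclusion.** The concern holds in a limited form. The plan adjusts one therapy contrast by two methods, without a common analysis set or estimand, and lets significance tests choose GLM covariates. Results by therapy may therefore refer to different patients and adjustments; that they certainly do cannot be shown.

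Matching is likely to cost precision: roughly 15–50% more variance than overlap weighting, least near an even split. That range rests on assumed 1:1 matching, a 0.2 SD caliper, a 20–50% smaller group and 240 evaluable patients all in one of the two groups; the article gives neither the therapy split nor the match ratio.

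A reader might also infer that the stated 87% power fails. It does not: it belongs to the triglyceride-target comparison and reproduces. The point touches a secondary objective and leaves the primary comparison alone. It is worth changing because the remedy is cheap.

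**What to change.** 1. Use one prespecified adjustment for OF-free days and every secondary outcome compared by therapy: overlap weighting on the propensity score, with robust standard errors.
2. Replace significance-selected covariates by a fixed list of prognostic baseline variables, the same for all these outcomes.
3. State that the estimate refers to patients with a real chance of either therapy. Keep matching, if wanted, as a sensitivity analysis.
4. Account for centre where feasible. With 240 patients in 30–40 hospitals the average is 240/40 = 6 to 240/30 = 8 per hospital, so a separate term for each is unlikely to be estimable; a random intercept or prespecified grouping of centres in the propensity model is more realistic. Robust standard errors clustered by centre address correlation, not confounding.
5. Enrolment period may be added as an optional covariate.

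The cost is analysis wording; no new data are needed. The target population changes somewhat and must be described, and centre or period terms use some degrees of freedom.

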## Methods

### Study Objectives

The primary objective of the study is to evaluate the relationship between TG decline and the evolution of organ failure in a cohort of early HTG-AP patients with worrisome features. The secondary objectives are to characterize the current clinical practice regarding TG-lowering therapy, describe the association between different choices of therapy and clinical outcomes. The third objective is to provide data for future trials. Accordingly, every secondary endpoint is also supposed to be hypothesis generating.

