### Exclusion Criteria

Failure to Obtain Informed Consent;Pregnant or Lactating Women; Or Have a Pregnancy Plan Within a Month After the Study (Including Male Subjects);Researchers' Family Members who Are Directly Involved in the Study;Patients Are Expected to die Within 48 H After Enrollment, Defined as Patients With Norepinephrine Usage at a Dose of 25 mg/min or More Under Full-Fluid Resuscitation, With a Systolic Blood Pressure <90 mm Hg and Serum pH Values <7.0. The Judgment Will be Made by the Treating Physician.

Informed consent should be sought for each participant or a patient's relative. They are free to withdraw from the study for any reason without the need for further explanation. This prospective observational study examines clinical outcomes in early HTG-AP patients with worrisome features treated with TG lowering therapy (from fasting to sophisticated blood purification). Therefore, no mandatory intervention or randomization is proposed. The main treatment modalities for TG-lowering therapy include fasting, medical treatment (either heparin, insulin, or both), and blood purification, including hemoperfusion, hemofiltration, and therapeutic plasmapheresis. The treatment is at the discretion of treating physicians.

We recommend all patients receive standard treatment that follows the “Acute Pancreatitis Treatment Guidelines” issued by the American College of Gastroenterology (ACG) in 2013 and the standard treatment plan for acute pancreatitis provided in the “Evidence-Based Guidelines for the Treatment of Acute Pancreatitis” issued by the International Association of Pancreatology (IAP) and the American Pancreatic Association (APA) (23, 24).

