### Data Collection and Management

A web-based electronic database (access through the website of the CAPCTG, https://capctg.medbit.cn/) is used for data collection and storage. All data are de-identified and input by the primary investigator or nominated investigators (less than two for each participating center) approved by the primary investigator, and a double check will be done by the research coordinator. Training for data entry is performed by the provider of the electrical database (Unimed Scientific, Inc, Wuxi, China) and the coordinating and data management center of the CAPCTG. Data including demographic characteristics, baseline characteristics, daily laboratory test, daily TG-lowering treatment, daily SOFA score, and follow-up characteristics. Demographic characteristics include age and sex. Baseline characteristics include body mass index (BMI), SOFA score on admission, Acute Physiology and Chronic Health Evaluation II (APACHE II) score on admission, the systemic inflammatory response syndrome (SIRS) on admission. Daily laboratory tests include serum total cholesterol (TC), triglyceride (TG), high-density lipoprotein cholesterol (HDL-c), low-density lipoprotein cholesterol (LDL-c), apolipoprotein A1 (Apo A1), apolipoprotein B (Apo B), apolipoprotein E (Apo E), lipoprotein a [LP(a)], free fatty acids (FFA), C-reactive protein (CRP), and procalcitonin (PCT). Daily TG-lowering treatment includes blood purification treatment (e.g., plasma exchange, hemoperfusion, and hemofiltration) and medical treatment (e.g., insulin and heparin). Follow-up characteristics include ICU days, hospital days, in-hospital cost, revision of the Atlanta classification on admission, CT severity index (CTSI) score (Based on the last image before discharge or death), mortality, and incidence of major complications on day 60. According to the schedule shown in Table 1, the investigators are required to collect data during the index admission and on day 60 after enrollment. And a follow-up on day 60 will be implemented through telephone.

**Table 1 T1:** Schedule of enrollment, assessment and follow up.

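### The secondary-outcome models adjust for severity at admission only if it differs significantly between groups, so a p-value can drop a true confounder

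*Protocol article*

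**What the plan says.** The Statistical Analysis section of the Protocol article limits the rule to one set of models: "For secondary outcomes, a multivariate analysis generalized linear model (GLM) model will be performed". These models relate each secondary outcome to TG decline and to TG-lowering therapy. The covariates come in two parts:

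- Three are fixed: "The variable included in the model will be age, sex, TG level at enrollment".
- The rest are "other baseline variables that have significant differences between groups".

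Data Collection and Management lists the severity measures recorded at baseline, including "SOFA score on admission, Acute Physiology and Chronic Health Evaluation II (APACHE II) score on admission", together with SIRS and BMI. None of these is among the three fixed covariates, so each depends on the second part.

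Three other statements set the context:

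- Under Exclusion Criteria: "The treatment is at the discretion of treating physicians".
- The TG groups are formed after enrolment, with patients "dichotomized depending on whether the TG level reaches 5.65 mmol/L on Day 3".
- Under Study Objectives, "every secondary endpoint is also supposed to be hypothesis generating".

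**The concern.** Confounding by a baseline variable depends on how far it differs between groups and on how strongly it predicts the outcome. A significance test of the baseline difference sees only the first of these, mixed with sample size. A strong predictor with a modest imbalance can fail the test and be left out, while an irrelevant variable with a chance imbalance gets in.

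This matters more here than in a randomised trial. Physicians choose the therapy, and the Statistical Analysis section itself expects prognostic characteristics to differ by therapy. Severity at admission is therefore an anticipated confounder, yet whether it is adjusted for is left to a p-value.

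No other stated analysis repairs this. Propensity score matching is described only for therapy against organ-failure-free days. The TG-decline comparison of the primary outcome is a Wilcoxon test, and no covariates are named for the supporting Fine and Gray model. The generalized linear model is the only TG-decline analysis with stated baseline covariates. At stake is whether the adjusted secondary estimates, meant to inform future trials, carry avoidable severity bias.

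**Working it through.** **Step 1. Group sizes, checked against the plan's power.** Sample Size Justification gives 240 evaluable patients (300 × 0.8) and power of 87% (2 days, SD 5) and 82.5% (1.5 days, SD 4). It states neither alpha nor the group ratio. Assume two-sided 0.05 and 120 v 120. The standard error of a difference in SD units is s = √(2/120) = 0.1291.

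- Φ(2/(5 × 0.1291) − 1.96) = Φ(1.138) = 87.25%; with the t distribution, 86.99%.
- Φ(1.5/(4 × 0.1291) − 1.96) = Φ(0.945) = 82.76%; with the t distribution, 82.46%.

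Both figures reproduce, so 120 v 120 is a fair working assumption.

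**Step 2. Further assumptions, none given in the documents.** The screen is at two-sided p<0.05. There is one confounder with a true imbalance of D standard deviations. The outcome is continuous and in days (ICU-free and hospital-free days are secondary outcomes on a 0–14 scale). It shifts by 2 days per SD of the confounder, with residual SD 4.5. The total outcome SD is then √(2² + 4.5²) = 4.92, close to the plan's 5. There is no true exposure effect.

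**Step 3. Chance of being dropped.** The observed imbalance d is approximately normal with mean D and standard error s. The variable is dropped if |d| < 1.96 × 0.1291 = 0.253. With a = (−0.253 − D)/s and b = (0.253 − D)/s, P(drop) = Φ(b) − Φ(a).

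**Step 4. Bias.** If the variable is dropped, the expected bias is 2 × d; if it is kept, zero. So the average bias is 2 × {D × P(drop) + s × [φ(a) − φ(b)]}, and the bias given dropping is that figure divided by P(drop).

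Worked case, D = 0.2: a = −3.509, b = 0.411, P(drop) = 0.659. Average bias = 2 × {0.2 × 0.659 + 0.1291 × (0.0008 − 0.3667)} = 0.17 days. Given dropping, 0.169/0.659 = 0.26 days.

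| True imbalance (SD) | Dropped | Average bias (days) | Bias when dropped (days) |
|---|---|---|---|
| 0.1 | 88% | 0.13 | 0.14 |
| 0.2 | 66% | 0.17 | 0.26 |
| 0.25 | 51% | 0.15 | 0.30 |
| 0.3 | 36% | 0.12 | 0.33 |
| 0.4 | 13% | 0.05 | 0.38 |
| 0.5 | 3% | 0.01 | 0.41 |

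Simulation of the same set-up agrees (0.16 to 0.17 days at 0.2 SD). Always adjusting gives a bias of about zero.

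**Step 5. Sensitivity.**

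- Unequal groups: at 3:1 with the same 240 patients, s = 0.1491. The drop rate is then 73% at 0.2 SD and 48% at 0.3 SD.
- Several confounders: with five independent ones at 0.2 SD, the chance that at least one is dropped is 1 − 0.341⁵ = 99.5%. SOFA, APACHE II and SIRS are likely to be correlated, so independence is an extreme case.
- Error rate: in simulations with outcome SD 5 and confounder–outcome correlation 0.3 or 0.5, type I error under the screen reached at most about 6% for one confounder.
- Scale: the standard error of the unadjusted difference is 4.92 × 0.1291 = 0.64 days, so an average bias of 0.17 days is about a quarter of one standard error.

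**The case against.** The strongest reply is that little depends on this rule. It governs secondary, hypothesis-generating models only. Most of those outcomes are binary, and the calculation in days does not apply to them directly. If severity is a strong driver of therapy choice or of reaching the TG target, its imbalance will probably be large, and the screen then almost always keeps it (97% at 0.5 SD). The average bias from one confounder stays under 0.2 days in the equal-group case.

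All of that stands and it limits the weight of the point. It does not defend the rule, which fails in the middle range where imbalance is modest and prognosis strong, and which offers nothing in return. Biases in the same direction from several dropped covariates would also add up.

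Two lesser complaints carry little weight. Letting in a variable unrelated to outcome costs mainly precision. Different adjustment sets for TG decline and for therapy are not in themselves wrong, since different exposures can have different confounders.

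A reader might also infer that each omission costs 0.4 to 0.5 days (0.2 or 0.25 × 2). That ignores selection: a variable is dropped only when its observed imbalance is small, and the bias given dropping is then about 0.25 to 0.30 days.

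**Conclusion.** The point holds as a defect in a rule that the plan states outright, not as a missing detail. In the secondary-outcome models, severity covariates beyond age, sex and enrolment TG are at the mercy of a baseline significance test. Under the assumptions above, a confounder imbalanced by 0.2 to 0.3 SD is dropped in about two thirds to one third of studies. The average bias is 0.12 to 0.17 days on a 0–14-day type of outcome, and the bias is about 0.25 to 0.30 days when a confounder at 0.2 to 0.25 SD is dropped. The imbalance, the covariate effect, the screening level and the group ratio are all assumed.

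Two stronger readings are not supported. The first is that the main result is biased by this rule: the primary outcome is compared by a Wilcoxon test, and therapy against that outcome goes through propensity score matching, so the stated rule does not reach either. The second is that all confounders are screened: three always enter. The change should be made because it is cheap and better, but the primary conclusion does not depend on it.

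**What to change.** In the Statistical Analysis section, replace the clause "other baseline variables that have significant differences between groups" with a pre-specified list: admission SOFA, APACHE II, SIRS and BMI, in addition to age, sex and enrolment TG, included in every secondary-outcome model whatever the baseline p-values. Add time from pain onset if it is recorded; it appears as a 72-hour eligibility limit but not among the variables in Data Collection and Management.

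The cost is one sentence, and the four added variables are already collected. The downside is a few more parameters, which matters for rare outcomes such as death, bleeding or fistula. For those, use a penalised (Firth-type) fit or a propensity score built from the same list.
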